### Sample size calculation

A mean difference of 6 on the primary clinical outcome measure (GAF) with a pooled study SD of 15 was observed in our previous trial in the same setting.^12^ A recent indicated minimum clinically important difference for the GAF in schizophrenia patients has been given as a mean difference of 4.^24^ A total sample size of 526, that is, 263 patients in each arm (recruited across 24 PHCs, with an average cluster size of 22 patients) has over 90% power to detect a mean difference of 6 and 85%–90% power to detect a more modest mean difference of 4 in the GAF given a two-tailed significance level of 0.05 and based on the following parameter assumptions: (1) baseline–outcome correlation of 0.5, repeated measures correlation of 0.7^25^ and loss to follow-up of 20% (patient-level parameters) and (2) intracluster correlation coefficient of 0.01^26^ and coefficient of variation in cluster sizes of 0.65 (PHC-level parameters).^27^ The primary endpoint for the GAF is the ‘average’ GAF across 6 and 12 months follow-up.

This sample size has 90% power to detect at least a 20% absolute difference in the treatment adherence rate between the intervention arm compared with the ETAU arm at 6 and/or 12 months follow-up based on two-tailed alpha of 0.025 (to account for multiple testing in respect of 6-month and 12-month testing). This is based on an observed ≈20% higher level of adherence within the intervention compared with ETAU arms in the original STOPS trial at 3 and 12 months follow-up,^11^ and further assuming the design effect PHC-level parameters as noted in (2) above. Thus, the study is adequately powered to detect significant differences (at the level of two-tailed alpha of 0.05 in each case) across the two distinct primary outcomes: (1) the primary clinical outcome (GAF) and (2) the primary process outcome (medication adherence).

### Trial management and monitoring

The STOPS+ trial will be monitored in line with the protocol and the trial standard operating procedures. An independent Trial Steering Committee (TSC) which will have service user representatives will monitor trial progress. The TSC is empowered to independently review the ethical and data management procedures. A Data and Safety Monitoring Board (DSMB) will be convened to ensure the safety of participants and the integrity of the data. The PHCs in the trial will receive training around safety reporting and additionally, participants and their family members will be informed of how to report concerns and safety issues, while they are participating in the trial. The Project Management Committee will be responsible for setting up the trial, ongoing management and monitoring, promotion of the study, training and the interpretation of the results.

### Safety and adverse events reporting

All adverse events and serious adverse events (SAEs) that are reported by the participant, family member or identified by the trial team or PHC staff members during the trial will be recorded and reported following trial safety reporting procedures. Related and unexpected SAEs will be reported to the local Research Ethics Committee, DSMB and TSC within 15 days. The DSMB will review all safety data and make any decisions regarding early termination of the study in line with their respective terms of reference.

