### The control: ETAU

Typically, in Pakistan, treatment for schizophrenia consists of accessing hospital-based psychiatric services with little to no involvement of PHC and a limited provision of medication from the hospital pharmacy. ETAU provided in the control clusters will include the treatment received by patients’ routine healthcare setting, which includes treatment provided by a psychiatrist in the outpatient clinics of the psychiatry department of the local hospital and brief counselling about the treatment and outcome of the disorder. Patients may be admitted to an inpatient unit at the hospital. This will be enhanced in the control cluster PHCs with training provided to PHC physicians in WHO Mental Health Gap Action Programme (MhGAP) (https://www.who.int/mental_health/mhgap/en/t) in addition to the regular and reliable provision of psychotropic drugs at the PHC. The patients will be informed that the antipsychotic medication is available in the PHC centre and they can access the centre for supply of medication. The PHC physician will have the option to liaise with the treating psychiatrist, as provided in the MhGAP guidelines.

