### STOPS+ intervention

The STOPS+ intervention will consist of the ETAU plus the following components.

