#### Supervision by a trained family member for dispensing and administering medication

A family member who is living with the patient for a minimum of 6 months prior to recruitment to the trial will be nominated by the patient. The family member will dispense medication, observe that is has been taken correctly and record this information on a simple sheet of paper designed and used in the previous STOPS trial.^9^ Family members will be reminded to administer the medication by an automated text message system, which will also request a response once the medication has been taken correctly. The text message reminders will be sent everyday for the first 3 months after starting the treatment. If the family member does not have access to a mobile phone, a handset and training in using it will be provided.

A multipurpose technician (MPT) from each PHC centre will provide training to family members for the storage and administration of the medication, recording when the medication has been taken correctly and the importance of maintaining the family dynamic.

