#### Treatment for schizophrenia at PHC level supervised by mental health professionals

Ongoing management and monitoring of the patient’s schizophrenia will take place at their PHC centre by the PHC physician, under the supervision of the treating psychiatrist with the help of the mobile technology platform smartphone for monitoring, assessment and remote treatment (SMART). SMART will provide two-way communication between mental healthcare professionals. One month’s supply of medication will be made available, via their PHC, to the family member. The automated messaging system will also remind the family member about collecting the following month’s supply.

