#### Monitoring the availability of essential psychotropic medication and their side effects

A kit to monitor the supply of medication will be used to monitor the availability and supply of psychotropic medication. This will consist of (a) a cupboard dedicated specifically for the storage of psychotropic medication, (b) a tracking sheet used to monitor the stock levels and (c) a simple checklist for monitoring side effects of antipsychotics.

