### Secondary outcomes

The details of secondary outcomes and the standardised instruments for measuring these are given in table 1. These instruments will measure secondary outcomes such as physical health outcomes, family/caregivers burden and internalised stigma.

**Table 1 T1:** Description of outcome measures and instruments

Domains measured	Measure
Sociodemographics	Age
	Gender
	Years in education
	Marital status
	Work status
	Mini-Neuropsychiatric Interview for diagnosis of schizophrenia^21^
Physical health	Body mass index
	Blood pressure
	Waist circumference
Primary outcomes	
Level of functioning	Global Assessment of Functioning^18^
Level of adherence	Treatment adherence rating scale^20^
Secondary outcomes	
Mental state and psychiatric symptoms	Brief Psychiatric Rating Scale^40^
Caregivers’ burden	Family Burden Scale^41^
Perceived stigma	Internalised Stigma of Mental Illness^42^
Side effects of antipsychotic medication	Glasgow Antipsychotic Side-Effects Scale^43^
Cost of care	Client Service Receipt Inventory^44^
Quality of life and cost-effectiveness	EuroQol (EQ5D)^45^
Illness severity, improvement and response to treatment	Clinical Global Impression Scale^46^
Drug use	DAST Drug Screening Tool^47^
Depression	Patient Health Questionnaire^48^
Suicide Ideation	Suicide Behaviours Questionnaire Revised^49^

DAST, Drug Abuse Screening Test; EQ5D, EuroQol 5 Dimension.

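### Adverse events are captured partly through PHC staff and relatives, who watch patients more closely in STOPS+ than in ETAU, so recorded counts can differ between arms through detection alone

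*Protocol article*

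**What the plan says.** Under Safety and adverse events reporting, one rule covers both arms: adverse and serious adverse events "reported by the participant, family member or identified by the trial team or PHC staff members during the trial will be recorded", following the trial's safety procedures. The DSMB then reviews all safety data and makes any decision on early termination under its terms of reference. The section does not say which safety measure is to be compared between arms.

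The arms are described as follows.

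- **STOPS+.** The section STOPS+ intervention opens: "The STOPS+ intervention will consist of the ETAU plus the following components". The components include a supply-monitoring kit containing "a simple checklist for monitoring side effects of antipsychotics". Continuing care "will take place at their PHC centre by the PHC physician", supervised by the treating psychiatrist, with medication supplied monthly to the relative. On the relative's task: "The family member will dispense medication, observe that is has been taken correctly and record this information on a simple sheet of paper".
- **ETAU.** The control section says: "This will be enhanced in the control cluster PHCs with training provided to PHC physicians in WHO Mental Health Gap Action Programme (MhGAP". It adds a dependable drug supply at the PHC and mentions no side-effect checklist. Usual care includes "treatment provided by a psychiatrist in the outpatient clinics of the psychiatry department of the local hospital". Patients may collect medication at the PHC, and the PHC physician's liaison with the psychiatrist is optional.

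Table 1 (Secondary outcomes) also lists the "Glasgow Antipsychotic Side-Effects Scale". All outcomes are measured in both arms at baseline, 6 and 12 months by research assistants (Duration of treatment and follow-up). Those assessors are masked to cluster arm and work away from the participating PHCs (Randomisation and allocation concealment).

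**The concern.** A count of spontaneously reported events is the product of how often events happen and how often someone notices and reports them. Here the second factor is altered by the treatment being tested. A patient seen regularly at a PHC that holds a side-effect checklist, with a relative trained to watch each dose, has more chances of having a tremor or sedation noted than a patient followed mainly in a hospital clinic. Hospital clinic and ward staff are not among the listed event sources.

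The DSMB is at risk of error in either direction. It could read an excess in STOPS+ as harm when it is only closer observation, or dismiss a true excess as closer observation because the sources cannot be told apart. Readers of the trial report would face the same difficulty with any table of events by arm.

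**Working it through.** The article states no adverse event rate, count or comparison, so there is no figure to reproduce. The check is mainly a comparison of the four event sources by arm.

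| Source | STOPS+ | ETAU |
|---|---|---|
| Participant | told how to report | told how to report |
| Relative | told how to report; also trained, observes and records doses, daily text reminders for 3 months | told how to report; no supervising role |
| PHC staff | safety-reporting training; also regular monitoring, monthly supply, side-effect checklist | safety-reporting training; mhGAP training; contact depends on the patient coming to the PHC |
| Trial team | 6- and 12-month visits | 6- and 12-month visits |

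Two of the four sources are described alike. For the other two, instruction is alike (Trial management and monitoring) but contact and observation are not.

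**Illustration of size.** Every detection and risk value below is an assumption; none is in the documents.

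1. Recorded proportion = true proportion × detection probability. With equal true risk, recorded risk ratio = detection in STOPS+ ÷ detection in ETAU.
2. From Sample size calculation: 263 patients per arm, average cluster size 22, intracluster correlation 0.01, coefficient of variation of cluster size 0.65. Design effect = 1 + ((0.65² + 1) × 22 − 1) × 0.01 = 1 + 30.295 × 0.01 = 1.303. Effective size = 263 ÷ 1.303 = 201.8 per arm. This carries the plan's intracluster correlation over to adverse events and ignores loss to follow-up.
3. ETAU detection is fixed at 0.50. The last column is the chance of a two-sided p<0.05 when the true risks are equal.

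| True risk | Detection in STOPS+ | Recorded, ETAU vs STOPS+ | Risk ratio | Extra recorded patients of 263 | Chance of p<0.05 |
|---|---|---|---|---|---|
| 20% | 0.60 | 10% vs 12% | 1.2 | 5 | 9% |
| 20% | 0.75 | 10% vs 15% | 1.5 | 13 | 33% |
| 20% | 0.90 | 10% vs 18% | 1.8 | 21 | 64% |
| 40% | 0.60 | 20% vs 24% | 1.2 | 11 | 16% |
| 40% | 0.75 | 20% vs 30% | 1.5 | 26 | 64% |
| 40% | 0.90 | 20% vs 36% | 1.8 | 42 | 95% |
| 60% | 0.60 | 30% vs 36% | 1.2 | 16 | 25% |
| 60% | 0.75 | 30% vs 45% | 1.5 | 39 | 88% |
| 60% | 0.90 | 30% vs 54% | 1.8 | 63 | >99% |

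With equal detection the ratio is 1.0 and the last column is 5%. The table shows that a moderate detection gap would matter. It does not show that this trial has one of that size.

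**The case against.** There is a fair case on the other side.

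- **No comparison is planned.** The safety section covers recording, expedited reporting and oversight, and Statistical analysis details between-group models only for the two primary outcomes. A reader might infer that the published safety comparison will be biased, but no such comparison is stated. What stands is narrower: the DSMB is given all safety data without being told which part is comparable between arms.
- **Detail may sit elsewhere.** Event forms, routing of checklist findings and DSMB tables normally belong in operating procedures and terms of reference, which are not shown. That is right, and the absence of those details is not the point. The unequal surveillance is itself stated in the article, and uniform reporting procedures would not equalise contact.
- **Both arms have reporters.** Safety training is not limited to one arm, every participant must have a willing family member, and ETAU patients can use the PHC. This narrows the gap but does not close it.
- **The comparable measure already exists.** Nothing excludes the Glasgow scale from the DSMB's review. This is correct, and it makes the remedy cheap. The safety section gives the scale no role, however.
- **Serious events are less exposed.** Deaths and admissions depend little on a side-effect checklist. This stands, and it confines the concern mainly to non-serious drug side effects.

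**Conclusion.** The point holds in a limited form. By design, two of the four adverse event sources observe patients more closely in STOPS+ than in ETAU. Recorded counts can therefore differ between arms through detection alone, most plausibly upward in STOPS+, and chiefly for non-serious drug side effects.

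A reader might go further and infer that STOPS+ will look more harmful than it is. The documents do not support that. They do not say that checklist findings enter the event record. They give no detection rates, so the ratios of 1.2 to 1.8 are only quotients of assumed values. Better adherence could also truly change side effects and relapse-related events, in opposite directions, so the net difference in counts is not fixed in sign.

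The primary outcomes are unaffected. The change is worth making because the DSMB uses these data for a consequential decision and the trial already collects a more comparable measure.

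**What to change.** Amend Safety and adverse events reporting in two respects.

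1. Name the Glasgow scale at 6 and 12 months, together with deaths and hospital admissions, as the main between-arm safety comparison for the DSMB and the trial report. The scale is already collected in both arms by masked assessors. Inpatient admissions are already covered by the service receipt inventory (Cost-effectiveness).
2. Record the source of each adverse event (PHC checklist, spontaneous report, assessor visit) and report events by arm and source. Show checklist-found events separately. Keep the pooled counts, but mark them as open to unequal ascertainment.

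The cost is one field on the adverse event form and some reporting text; no new assessment is needed. There are two downsides. Pooled counts carry less weight as a between-arm result. The Glasgow scale is also imperfect: it rests on reports from participants who know their arm, and it misses those lost to follow-up, for which the sample size allows 20%.

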### Data management

All data will be managed in line with the protocol and will be stored securely following the KMU and Keele University standard policy on data storage and confidentiality. Individual participant data will be pseudonymised through the use of a unique study ID and will be stored securely and separately from any identifiable data. Access to data will be restricted to members of the research team. Outcome data will be entered into an electronic database which will be stored on an encrypted secure network at KMU requiring a password to access. Data entry will be quality checked and coded using standard processes.

### Statistical analysis

Statistical analysis will be performed blind to cluster allocation. Primary analysis will be on an intention-to-treat (ITT) basis, with all participants analysed in their cluster. Between-group differences for both primary outcome measures (GAF and medication adherence) will be analysed using longitudinal mixed models that accommodate clustering at the (upper/hierarchical) practice level as well as repeated outcome measurements across three time points (baseline, 6 and 12 months) per participant, that is, linear/logistic mixed models for numerical and categorical outcomes, respectively, including PHC and participant as random factors. These models will be used to quantify the absolute between group difference in the primary clinical outcome (GAF) and odds ratio (and extracted absolute difference) for the primary process outcome (% adherence)—using linear and logistic models, respectively. For the GAF, the primary endpoint is the ‘average’ GAF over 6 and 12 months using available and modelled data to estimate the combined summary average mean difference in GAF between treatment arms over the 6-month and 12-month timeline; statistical significance in this case being given against two-tailed p=0.05. Though the ‘average’ is the single primary endpoint for the GAF, we will also evaluate the treatment-by-time interaction to give estimates of between-arm mean differences at the individual 6 and 12 months follow-up time points (secondary endpoints).

For medication adherence, between-group comparison at both 6 and 12 months is primary (derived through treatment-by-time interaction within the generalised mixed model)—hence, the requirement to take into account the multiple testing by assessing significance against a more conservative two-tailed p=0.025. Estimates of between-group mean differences will be given including 95% CIs and p values. The mixed models (detailed above) will be adjusted for age, gender, baseline GAF score and corresponding baseline score of the outcome being measured as individual-patient-level covariates, PHC-level characteristics (PHC size), stratification variable (rural/urban) and a random effect for the PHC. Mixed-model analysis fulfils the ITT principle with missing data being accounted for under the missing at random assumption.

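### Adherence at 6 and 12 months is tested at a fixed 0.025 each; this is valid, but Holm's rule keeps the same 0.05 bound and would claim an effect at both times more often

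*Protocol article*

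**What the plan says.** For the adherence outcome, the Statistical analysis section of the protocol article states that "between-group comparison at both 6 and 12 months is primary". Each comparison comes from the treatment-by-time interaction of the mixed model and is judged by "assessing significance against a more conservative two-tailed p=0.025". The same section plans 95% confidence intervals and p values.

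The Sample size calculation section matches this. Power for adherence is "based on two-tailed alpha of 0.025 (to account for multiple testing in respect of 6-month and 12-month testing", and each of the two primary outcomes is held overall "at the level of two-tailed alpha of 0.05 in each case". The power claim reads "This sample size has 90% power to detect at least a 20% absolute difference in the treatment adherence rate", and the difference is to be seen "at 6 and/or 12 months follow-up".

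The article does not name the method, but splitting 0.05 equally over two tests is Bonferroni. It describes no step-down or other sequential rule.

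**The concern.** Under the fixed split, once one time point has passed at 0.025 the other must still pass at 0.025. Holm's rule lets it be tested at 0.05 at that stage, with no further assumption and the same family-wise bound. Take p = 0.001 at 6 months and p = 0.03 at 12 months. The plan as written would report 12 months as a primary comparison that was not significant, although the 5% allowed for this outcome permits the claim. Because the article calls both comparisons primary, evidence at both times is of interest, and the fixed split makes it somewhat harder to obtain than it needs to be.

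**Working it through.** **Inputs from the Sample size calculation section.** 263 per arm, 24 centres, mean cluster size 526/24 = 21.9 (given as 22), ICC 0.01, coefficient of variation of cluster size 0.65, 20% loss, 20-point difference, two-tailed 0.025 per test, 90% power.

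**Assumed inputs.**
- Control adherence rate: not given for the power calculation. 40-50% is used; the Introduction cites non-adherence of about 50%.
- Correlation between the 6- and 12-month test statistics: not given for adherence. 0.5-0.7 is used, with 0 to 0.9 as the range; 0.7 is the repeated-measures value assumed for the GAF.

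**Step 1: reproduce the stated power.**
- Design effect = 1 + ((CV² + 1)m − 1) × ICC = 1 + (1.4225 × 21.9 − 1) × 0.01 = 1.302.
- Effective n per arm = 263 × 0.8 / 1.302 = 161.6.
- Power at 0.025 (normal approximation, pooled variance under the null): 91.7% for 40% v 60%, and 92.8% for 50% v 70%.
- A t test with 22 degrees of freedom gives 88.8% and 90.1%.
- With a continuity correction, 40% v 60% needs 163 effective patients per arm; 163 × 1.302 / 0.8 = 265, against 263 stated.

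The stated 90% is therefore reproduced. The alpha split also adds up: 0.025 + 0.025 = 0.05.

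**Step 2: compare the two rules.** The two test statistics are taken as bivariate normal. The critical values are 2.241 (0.025 two-tailed) and 1.960 (0.05 two-tailed). Power of 90% at 0.025 means an expected statistic of 2.241 + 1.282 = 3.523 at each time. The fixed rule claims both times if both statistics exceed 2.241. Holm claims both if the larger exceeds 2.241 and the smaller exceeds 1.960.

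| Correlation | Both times, fixed 0.025 | Both times, Holm | Gain (points) | At least one time, either rule |
|---|---|---|---|---|
| 0 | 81.0% | 88.4% | 7.4 | 99.0% |
| 0.5 | 83.2% | 89.4% | 6.1 | 96.8% |
| 0.7 | 84.7% | 90.1% | 5.4 | 95.3% |
| 0.9 | 86.9% | 91.1% | 4.2 | 93.1% |

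(Gains are taken before rounding.) The last column is the same for both rules because each declares any effect at all only when the smaller p value is below 0.025.

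**Step 3: use the protocol's own design inputs.** With control rates of 40-50%, 20% loss, the design effect above and unpooled variances, power per time is 92.3-93.4%. At correlation 0.5-0.7, the chance of claiming both times is about 87-90% with the fixed rule and 92-94% with Holm, a gain of 4 to 5 points.

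**Step 4: unequal effects.** With power of 90% at one time and 60% at the other, and correlation 0.7, the chance of claiming both is about 59% with the fixed rule and 69% with Holm.

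**Step 5: error rate.** With no effect at either time, the family-wise error is the same for both rules: 0.049, 0.043 and 0.036 at correlations 0, 0.7 and 0.9. With no effect at one time and 90% power at the other, it is 0.025 for the fixed rule and 0.039-0.047 for Holm. Every value is within 0.05.

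**The case against.** The strongest reply is that nothing in the plan is wrong. The 0.025 threshold is valid, prespecified and the same in both sections, and the sample size was set on it. That stands. A reader might infer that the rule is a mistake or that the trial is underpowered for adherence. The documents do not support this, since the 90% is reproduced at 0.025.

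Secondly, a reader might infer that both times must succeed. The protocol does not say so: its power statement refers to a difference "at 6 and/or 12 months follow-up", and on that criterion Holm gains nothing. If success at both times were required, no split would be needed. Testing each at 0.05 would then give 89.7-90.6% at correlation 0.5-0.7 on the inputs of Step 2. Holm's benefit is confined to the second claim once a first has been made.

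Thirdly, a reader might take Holm's actual error to be identical. Only the 0.05 bound is identical; when one null is true, Holm uses more of it (Step 5). That is legitimate but should be stated.

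Fourthly, pairing Holm with 97.5% intervals would be awkward. In every case where Holm adds a claim, the second p value lies between 0.025 and 0.05, so a 97.5% interval would include no effect beside a significant result. This objection also stands, and it is why the planned 95% intervals should be kept.

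Finally, recruitment began on 1 November 2019, so relaxing a published primary threshold is more than an editorial change.

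**Conclusion.** The point holds as a minor, optional improvement. Holm is never less powerful than the fixed split and keeps the 0.05 bound under any correlation. At the stated 90% power per time, the chance of claiming both times rises from about 83-85% to 89-90% (correlation 0.5-0.7 assumed). The size of the gain depends on that assumed correlation and, where the protocol's design inputs are used, on an assumed control rate of 40-50%. Its direction depends on neither. The power for at least one time and the total of 526 are unaffected.

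**What to change.** In Statistical analysis, replace the fixed threshold for adherence with a sentence to this effect: the smaller of the 6- and 12-month p values is tested at two-tailed 0.025 and, if it is significant, the other is tested at 0.05. Report Holm-adjusted p values: twice the smaller p value (at most 1), and for the other the greater of that figure and its own p value. In the example above these are 0.002 and 0.03. Keep the planned 95% confidence intervals, which agree with the second-step test at 0.05, and state that they are not adjusted for multiplicity.

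The cost is one sentence and an amendment documented before unblinding, with no extra patients. One small mismatch remains: if the smaller p value lies between 0.025 and 0.05, nothing is declared significant although a 95% interval excludes no effect. The current plan already has this mismatch, for any p value in that range.

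### Adherence is tested at two-tailed 0.025 but the only interval level given is 95%, so a reported interval can exclude no effect beside a negative primary test (minor)

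*Protocol article*

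**What the plan says.** All of this stands in two sections of the protocol article.

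- **Statistical analysis, adherence.** "For medication adherence, between-group comparison at both 6 and 12 months is primary", and the plan will "take into account the multiple testing by assessing significance against a more conservative two-tailed p=0.025". The effect measure is an "odds ratio (and extracted absolute difference) for the primary process outcome (% adherence").
- **Statistical analysis, reporting.** The sentence straight after the 0.025 rule reads: "Estimates of between-group mean differences will be given including 95% CIs and p values". No other confidence level appears in the section.
- **Statistical analysis, GAF.** The single primary endpoint is the average over 6 and 12 months, with "statistical significance in this case being given against two-tailed p=0.05".
- **Sample size calculation.** Adherence is powered at 90% for a 20-point absolute difference, "based on two-tailed alpha of 0.025 (to account for multiple testing in respect of 6-month and 12-month testing"). The section closes by claiming adequate power for each primary outcome "at the level of two-tailed alpha of 0.05 in each case".

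**The concern.** For GAF the test level (0.05) and the interval level (95%) correspond. For adherence they do not: the alpha is split over two time points and the interval level does not follow it. Adherence is the only primary outcome with a split alpha, so the mismatch is confined to it.

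This is not a detail left to an analysis plan. The article states an interval level, and it does not match the test level stated one sentence earlier. At stake is how a borderline result on a primary outcome would look in the results table: an interval that excludes an odds ratio of 1, or a difference of 0, next to a conclusion that the comparison did not reach significance.

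**Working it through.** **Inputs from the article.** Two primary adherence comparisons; 0.025 two-tailed for each; 0.05 for the outcome as a whole; 90% power for a 20-point difference; 263 patients per arm in 24 centres (526/24 = 21.9 per centre); 20% loss to follow-up; ICC 0.01; coefficient of variation of cluster size 0.65. The control-arm adherence rate behind the power statement is not given, so it is an assumption here, and control rates of 30% to 70% were tried.

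**1. The plan's own figures.** Alpha: 0.05/2 = 0.025, a Bonferroni split, as stated.

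Power: design effect = 1 + ((1 + CV²)m − 1) × ICC = 1 + (1.4225 × 21.9 − 1) × 0.01 = 1.302. Effective patients per arm = 263 × 0.8 / 1.302 = 161.6. At alpha 0.025 the power is 91.7% for 40% v 60%, the lowest case tried, and 92.8% for 50% v 70%. The stated 90% is reproduced and slightly conservative.

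**2. Where interval and test part company.**

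| | Two-tailed level | Critical value |
|---|---|---|
| Planned adherence test | 0.025 | 2.241 |
| Stated 95% interval | 0.05 | 1.960 |
| Matching 97.5% interval | 0.025 | 2.241 |

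For 1.960 < |z| < 2.241, that is p between 0.025 and 0.05, the 95% interval excludes no effect and the test is negative. The matching interval is wider by 2.241/1.960 = 1.144, or 14%.

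**3. How often, per time point.** With θ the true effect in standard errors, the chance is Φ(2.241 − θ) − Φ(1.960 − θ). The opposite tail is negligible for the non-zero effects below.

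- No effect: 0.05 − 0.025 = 2.5%, counting both tails.
- θ = 2.2: Φ(0.041) − Φ(−0.240) = 0.516 − 0.405 = 11%.
- Stated 90% power at 0.025: θ = 2.241 + 1.282 = 3.52, so Φ(−1.282) − Φ(−1.563) = 0.100 − 0.059 = 4.1%.

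The third figure needs no control rate. It does take the 90% as power at each time point.

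**4. An illustration on the absolute scale.** Assume 40% v 60% and use the cluster size after dropout (21.9 × 0.8 = 17.5). The design effect is then 1.239 and the effective number per arm 263 × 0.8 / 1.239 = 169.8. SE = √((0.24 + 0.24)/169.8) = 0.053. Observed differences of about 10.4 points (1.960 × SE) to 11.9 points (2.241 × SE) fall in the band. At p = 0.035 (z = 2.108) the difference is 11.2 points, with

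- 95% interval: 0.8 to 21.6;
- 97.5% interval: −0.7 to 23.1.

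With this effective number and control rates of 40% to 60%, the chance per time point is about 11% for a true difference of 10 points. For a true difference of 20 points it is 1.5% to 3%, below the 4.1% of step 3 because power at these rates exceeds 90%.

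**The case against.** The case on the other side is substantial, and much of it stands.

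- **The decision rule is clear.** Significance is "assessing significance against a more conservative two-tailed p=0.025" in the analysis section, with the same level and reason in the sample size section, and p values will be printed beside the intervals. This stands.
- **Stronger readings that the article does not support.** A reader might infer that 95% intervals undo the multiplicity control. If the two intervals were themselves used as tests, the family-wise error would be 1 − 0.95² = 9.75% for independent comparisons (8.4% at a correlation of 0.7). The plan never says that inference is read from the intervals, so the formal error rate stays where 0.025 puts it. A reader might also object that two 95% intervals lack 95% joint coverage. The plan promises none, and each interval keeps its nominal coverage at its own time point.
- **The reporting sentence speaks of mean differences.** That fits GAF better than an odds ratio, and it may be meant as a general statement. It is a fair caveat on how firmly the sentence binds adherence. But it directly follows the adherence rule, adherence is also to be reported as an absolute difference, and no other level is offered. If adherence is not covered, its interval level is unclear and the same short clarification is needed.
- **Unadjusted 95% intervals beside an adjusted test are common.** They are acceptable when labelled as unadjusted. Here there is no label. A label alone would remove the risk of misreading, though not the disagreement between interval and verdict.

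**Conclusion.** The point holds as a minor but real inconsistency on a primary outcome. The article fixes 0.025 for each adherence test and gives 95% as its only interval level, and the two disagree for every p between 0.025 and 0.05. Type I error, sample size and power do not change.

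The chance of a discordant pair is about 4% per time point at the stated 90% power and about 11% if the true effect is near 2.2 standard errors. These figures rest on normal-theory intervals and tests built from the same estimate and standard error. The 4% also assumes that the 90% applies to each time point; the article's phrase covers 6 and/or 12 months and does not settle this. Figures tied to particular adherence rates are illustrations only, since the article gives no control rate for its power statement. That the mismatch exists depends on none of these assumptions except that interval and p value come from the same analysis.

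**What to change.** In the Statistical analysis section, state that the between-arm adherence contrasts at 6 and 12 months, as odds ratio and as absolute difference, will be reported with 97.5% confidence intervals to match the 0.025 tests, and that average GAF keeps 95%. If 95% intervals for adherence are shown as well, label them as not adjusted for multiplicity and say that significance rests on p<0.025. If the alpha rule for adherence is ever changed, the interval level should follow it.

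The cost is one phrase in the text and adherence intervals 14% wider on the analysis scale. Correspondence with the test is exact on the scale on which the model is tested (the log odds ratio); for the absolute difference extracted from that model it is close but not guaranteed at the margin.
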